## 1. Background

Adolescent idiopathic scoliosis (AIS) is a complex three-dimensional spinal deformity of unknown etiology, defined as a spinal curvature of  $\geq 10^{\circ 1, 2}$ . According to scoliosis screening studies conducted between 1985 and 2011, the prevalence of AIS is estimated to be between 0.5% and 5.2%. It is generally accepted that the incidence of AIS among individuals under the age of 16 is approximately 2% to 3%. Among adolescents with a Cobb angle greater than  $20^{\circ}$ , the likelihood of disease progression is 70% or more. According to the recommendations of the International Society on Scoliosis Orthopaedic and Rehabilitation Treatment (SOSORT), conservative treatment should be provided to adolescents with AIS to prevent the progression of scoliosis before skeletal maturity is reached.

Physiotherapy Scoliosis-Specific Exercises (PSSE) are among the most crucial conservative treatments for patients with AIS. Moderate-certainty evidence from multiple randomized controlled trials (RCTs) supports the effectiveness of PSSE in slowing the progression of scoliosis in AIS patients and even reducing the degree of curvature. However, compared to conventional exercises such as resistance training, PSSE requires a deeper understanding by patients of the specific exercises tailored to their type of scoliosis, making mastery more complex and challenging for AIS patients. Additionally, patients with AIS must adhere consistently to a standardized PSSE regimen over the long term and develop habits of daily self-management to ensure the efficacy of PSSE. In previous high-intensity evidence-based trials, the traditional PSSE model involved an initial assessment and 1 to 3 treatment sessions conducted by qualified physiotherapists at outpatient clinics or specialized orthopedic institutions, after which patients completed the PSSE regimen at home without supervision.

However, the traditional PSSE model faces several challenges. On one hand, due to the scarcity of medical resources—including specialized therapists and facilities—as well as limitations in time, cost, and transportation, a significant proportion of adolescents with AIS are unable to access professional guidance. On the other hand, due to a lack of awareness of the importance of home-based self-efficacy, AIS patients often fail to complete their home-based self-efficacy programs and do

not develop habits of daily self-management, resulting in sub-optimal outcomes in home-based self-efficacy training.

Digital interventions hold significant potential in overcoming these challenges, enhancing individual adherence and empowerment, and aiding individuals in managing their daily posture and completing PSSE training programs in a timely manner. However, few studies have explored the effectiveness of digital interventions in PSSE programs and daily posture management for AIS patients.

The Healbone Intelligent Rehabilitation System (HIRS) is a user-centered smartphone application that integrates remote supervision and guidance of PSSE training with scoliosis-related educational videos and articles. In our previous work, we demonstrated the efficacy of the HIRS system in patients with nonspecific low back pain. The purpose of this RCT is to compare the treatment outcomes of a Digital Care Group (DCG) receiving PSSE supervision and guidance through the HIRS system (Beijing, CN) and educational videos with those of a Conventional Intervention Group (CIG) following the traditional PSSE model.

## **2.Research Objective**

The Healbone Intelligent Rehabilitation System (HIRS) is a user-centered smartphone application that integrates remote supervision and guidance of PSSE training with scoliosis-related educational videos and articles. In our previous work, we demonstrated the efficacy of the HIRS system in patients with nonspecific low back pain. The purpose of this RCT is to compare the treatment outcomes of a Digital Care Group (DCG) receiving PSSE supervision and guidance through the HIRS system (Beijing, CN) and educational videos with those of a Conventional Intervention Group (CIG) following the traditional PSSE model.

## **3.Reseach Method**

This study is a single-center, parallel-group, randomized controlled trial conducted in accordance with the requirements of the Declaration of Helsinki. The study adheres to the CONSORT guidelines

### **3.1 Primary Outcome** : The change of the Cobb angle

## 3.2 Secondary Outcome :

- (1) The change of the angle of trunk rotation, ATR ;
- (2) The changes in pelvic tilt angle during the gait cycle between baseline and the 6-month follow-up.
- (3) Engagement metrics of participants.
- (4) The population of AIS patients with progression and improvement of Cobb angle of the major curve

## 3.3 The definition of outcomes

All subjects will undergo baseline measurements at the Department of Rehabilitation, Peking Union Medical College Hospital. After a 6-month intervention, all participants are required to return to the hospital for a 6-month follow-up assessment. The primary outcome measure is the change in the Cobb angle of the primary curve between baseline and the 6-month follow-up. The Cobb angle will be measured on standing radiographs by two physical therapists (PTs) who will determine the angle between the most tilted vertebrae at the upper and lower ends of the curve. The final Cobb angle will be the average of the two measurements. Secondary outcomes are listed in Table 5.

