## **4.3 Statistical Method**

The distribution of continuous variables was assessed using the Kolmogorov-Smirnov test, followed by verification through histograms and Q-Q plots. Demographic data were presented as mean (standard deviation) for continuous variables and as number (percentage) for categorical variables. Baseline demographic characteristics and engagement metrics between groups were compared using independent samples t-test or Mann-Whitney U test for quantitative variables, and Chi-square test or Fisher's exact test for categorical variables.

The effects of each intervention on primary and secondary outcomes were evaluated based on the 6-month endpoint outcomes and the changes between baseline and 6 months. Both intention-to-treat (ITT) and per-protocol analyses were conducted for outcome assessment. Missing data were handled using multiple imputation by chained equations (MICE).

Receiver operating characteristic (ROC) curve analysis was employed to determine the minimal clinically important difference (MCID) for improvement in Cobb angle post-PSSE intervention at 6 months, which was identified as 3.50 degrees. However, Charalampidis A et al. defined treatment success in patients with moderate idiopathic scoliosis as no progression in scoliosis in individuals with a Risser grade  $\leq 4$  after 6 months of PSSE intervention.

The primary and secondary outcomes of this study were reported as mean, standard deviation (SD), and 95% confidence interval (CI). Given the assumption of normality, primary and secondary outcomes were evaluated using the independent samples t-test. The proportion of patients who exhibited disease progression or improvement in Cobb angle between the two groups was compared using the Chi-square test.

179 All analyses were conducted under a two-tailed hypothesis with an alpha level of  
180 0.05. Statistical analyses were performed using SPSS (version 23.0, SPSS Inc.,  
181 Chicago, Illinois, USA), and were carried out by a blinded statistician

182

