## 194 **4.5 The method of Allocation**

195 Participants were randomly allocated to either the TBEG group or the OBEG group  
196 using an online platform (<https://www.random.org/>). Subsequently, subjects in the  
197 OBEG group were assigned the letter "C," while those in the TBEG group were  
198 assigned the letter "T." Based on the results generated by the online platform (e.g.,  
199 C, T, C, T, T, C, ...), slips of paper labeled with the letters "T" and "C" were  
200 placed in sealed, opaque, and uniformly sized envelopes. After all baseline  
201 measurements were completed for the study subjects, the envelopes were  
202 sequentially opened to reveal the allocation results. The allocation sequence was  
203 prepared by an independent researcher, not involved in the study, using a block  
204 randomization model. Given the nature of the intervention, it was not feasible to  
205 blind the physical therapists and patients to the allocation results.

206

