### 234 **6.3 Intervention**

235 In this trial, HIRS system will be provided free of charge to AIS patients in the DCG  
236 group, and physical therapists will encourage timely usage of the HIRS system via

smartphone during the six-month study period. HIRS is a smartphone application available for iOS, Android, and local web solutions. For participants without internet access, hotpots will be provided. The HIRS system consists of three distinct components: the physician's interface, the user's interface, and the data storage module, as depicted in Figure 2. A secure and seamless bidirectional connection is established between the physician's interface and the user's interface, supported by technical experts and IT professionals. The study involves two senior rehabilitation therapists, each with over five years of experience in the diagnosis and conservative management of scoliosis. One of the therapists is a member of SOSORT.

Prior to the commencement of the trial, professional healthcare personnel creates specific PSSE training videos, which, along with detailed instructions, were uploaded to the HIRS system. At the start of the trial, the HIRS system was installed on the smartphones of patients in the DCG group, and personal accounts will be registered via the application. During the initial treatment phase, therapists will transmit digital PSSE training protocols to the patients' personal accounts and provide education on the correct usage of the application. Patients are required to access the application via their personal accounts each time they engaged in PSSE training. Upon initiation of the exercises, patients will follow the instructions provided in the video to complete each movement in the training protocol. If a patient failed to engage in the exercises, the system automatically sends a reminder and notifies the PTs, who then contact the patient to determine the cause of non-compliance.

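### Nothing in the protocol masks the physical therapists who read the primary Cobb angle, so the 6-month reading may be made with knowledge of the arm

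*Protocol*

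**What the plan says.** Protocol section 3.3 defines the primary outcome: "The primary outcome measure is the change in the Cobb angle of the primary curve between baseline and the 6-month follow-up". The same section names the readers, "The Cobb angle will be measured on standing radiographs by two physical therapists (PTs) who will determine the angle", and the way their readings are combined: "The final Cobb angle will be the average of the two measurements". It says nothing about whether the readers know the arm or the visit.

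Section 4.5 states that, because of the nature of the intervention, it was not feasible to "blind the physical therapists and patients to the allocation results". It makes no exception for therapists who act as outcome readers. The same section has the envelopes opened only once baseline measurements are complete, and section 6.1 lists the Cobb angle among those measurements.

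The one blinded role named is in section 4.3, which says of the analyses "and were carried out by a blinded statistician". Section 6.3 describes physical therapists training patients in both arms and contacting digital-arm patients who do not exercise. It also says "The study involves two senior rehabilitation therapists, each with over five years of experience".

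**The concern.** The primary outcome is measured by members of the professional group that the protocol says could not be blinded. The reason given for not blinding applies to delivering treatment. It does not apply to reading a stored radiograph, which does not show whether the patient used an app or attended outpatient sessions.

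Reading a Cobb angle calls for judgement, because the reader must pick the most tilted vertebra at each end of the curve. The trial also has an expected direction: section 4.2 states the alternative that the digital arm does better, and section 1 reports earlier success of the system in low back pain. If readers know the arm at 6 months, even a small unconscious tendency adds to the estimated treatment effect. A blinded statistician cannot remove it afterwards. The progression and improvement categories in the secondary outcomes use the same readings. Since any increase counts as progression, small shifts near zero can also move patients between categories.

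**Working it through.** **Step 1. Is there any masking of the readers?** The relevant places, side by side:

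| Place | What it settles |
|---|---|
| 3.3 | Readers are two physical therapists; no masking to arm or visit |
| 4.3 | The statistician is blinded |
| 4.5 | Physical therapists and patients not blinded; baseline measured before envelopes are opened |
| 6.3 | Physical therapists deliver treatment in both arms |
| 7 | Cobb angle measured again at the hospital after 6 months; no reader conditions |

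No section masks the readers or keeps them apart from treatment.

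**Step 2. Where can knowledge of the arm enter?** Write improvement as baseline reading minus 6-month reading. As planned, the baseline reading precedes allocation, so the arm cannot affect it. Let the 6-month readings be shifted on average by e(DCG) in the digital arm and e(CIG) in the conventional arm. Then

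expected difference in mean improvement = true difference + [e(CIG) − e(DCG)].

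No matching baseline shift is subtracted, so the net shift b = e(CIG) − e(DCG) enters in full. With two readers whose net shifts are b1 and b2, the average carries (b1 + b2)/2. If both share the same expectation, this equals b. Averaging reduces random reading error but not a shared shift.

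**Step 3. Size, for illustration.** The protocol gives no figure for reading bias, so there is none to reproduce, and b is assumed over a range. The inputs from section 4.4 are SD 6 in each group, 51 evaluable per group (64 enrolled) and two-sided alpha 0.05. The planned 51 is taken as it stands; how it was derived does not bear on this point.

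Standard error of the difference: SE = 6 × √(2/51) = 1.19°.

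Type I error with no true effect: P(reject) = 1 − Φ(1.96 − b/SE) + Φ(−1.96 − b/SE).

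Example, b = 1°: b/SE = 0.84. The upper tail is 0.1317 and the total 0.1343.

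| Assumed net shift b | b/SE, 51 per group | Normal approximation, 51 per group | t-test, 51 per group | t-test, 64 per group |
|---|---|---|---|---|
| 0° | 0 | 5.0% | 5.0% | 5.0% |
| 0.5° | 0.42 | 7.1% | 7.0% | 7.5% |
| 1° | 0.84 | 13.4% | 13.3% | 15.5% |
| 1.5° | 1.26 | 24.3% | 24.0% | 28.9% |
| 2° | 1.68 | 39.1% | 38.5% | 46.5% |

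The last column assumes that nobody drops out, against the planned 20%, so the 51-per-group columns are the relevant ones. A shift of 1° is a quarter of the 4° difference that section 4.4 calls clinically meaningful (1/4 = 0.25).

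**The case against.** The strongest reply is that the protocol never says the readers know the allocation. The statement in section 4.5 is tied to the nature of the intervention and reads most naturally as being about therapists who treat. A reader might infer that the two Cobb readers are the two senior therapists of section 6.3, because the number is the same, and so conclude that the primary outcome is read unmasked by treating staff. The documents do not support that. The sentence in section 6.3 belongs to the description of the intervention and is never linked to radiograph reading. This part of the objection stands: unmasked reading is possible under the text but not established.

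There is also a real safeguard, since baseline measurements come before the envelopes are opened. It confines the arm-related exposure to the 6-month reading. It does not remove the problem, because a shift in that reading alone still passes into the change score, as Step 2 shows.

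Third, the type I error figures depend on shifts that are assumed. They show what would follow from a persistent net shift, not that one exists, and the upper values should not decide how serious the point is. That also stands.

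Finally, masking is not free, and coding films may not fully mask a therapist who has treated the patient, because the curve itself may be recognised. The fix has to allow for both.

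**Conclusion.** The point holds as a gap in the design. Sections 3.3 and 4.5 together leave the primary outcome with readers from a group declared unblinded, and no other section masks them or separates them from treatment. The 6-month reading may therefore be made with knowledge of the arm, and any resulting shift would carry over undiminished to the primary comparison.

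The documents do not show that the readers know the arm, that they are the treating therapists, or that the result will be biased. On size, under the protocol's SD of 6 with 51 per group and no true effect, an assumed net shift of 0.5° to 2° would raise the two-sided type I error from 5% to between about 7% and 39%. With no shift it stays at 5%. Confidence is high that masked reading is not specified; the amount of bias is unknown. The matter deserves correction before the study readings are made, because it concerns the sole primary outcome and analysis cannot repair it later.

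**What to change.** In section 3.3, state that:

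- all baseline and 6-month radiographs are stripped of name, group and date, then coded and shuffled by someone other than the readers, who holds the key;
- after follow-up is complete, the two physical therapists read the coded films independently of each other, using therapists who did not treat the patient where existing staff allow;
- the readings are locked before the code is broken.

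In section 4.5, limit the statement that blinding was not feasible to the delivery and receipt of treatment. If masked reading is already intended, these two edits are enough to say so.

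The cost is modest but not nil. Up to 256 films (128 participants × 2 visits) must be coded and read. Baseline films already read for eligibility or baseline assessment are read a second time, and the study readings wait until follow-up ends. The sample size does not change. Some risk remains that a treating therapist recognises a film, which is why readers outside treatment are preferable where available.

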### Study secondary outcomes (clinical and engagement)

| Outcome measure                                                                                  | Description                                                                                                                                                                                                                                                                                                                                                                                    |
|--------------------------------------------------------------------------------------------------|------------------------------------------------------------------------------------------------------------------------------------------------------------------------------------------------------------------------------------------------------------------------------------------------------------------------------------------------------------------------------------------------|
| The population of AIS patients with progression and improvement of Cobb angle of the major curve | The research team defines a reduction in the primary curve Cobb angle of 0° to 5° as "mild improvement," a reduction of more than 6° as "substantial improvement," and an increase in the primary curve Cobb angle as "progression." This study analyzed the populations of AIS patients in the DCG and CIG groups in terms of progression, "mild improvement," and "substantial improvement." |
| The improvement in the angle of trunk rotation (ATR)                                             | To evaluate the improvement in vertebral rotation at the spinal level in patients with AIS (Idiopathic Scoliosis) based on ATR (Angle of Trunk Rotation) improvement at baseline and 6-month follow-up, the following procedure is conducted:                                                                                                                                                  |

|                                                                                                           |                                                                                                                                                                                                                                                                                                                                                                                                                                                                                                                                                                                                                                                                                                       |
|-----------------------------------------------------------------------------------------------------------|-------------------------------------------------------------------------------------------------------------------------------------------------------------------------------------------------------------------------------------------------------------------------------------------------------------------------------------------------------------------------------------------------------------------------------------------------------------------------------------------------------------------------------------------------------------------------------------------------------------------------------------------------------------------------------------------------------|
|                                                                                                           | 
The subject is asked to stand with feet shoulder-width apart, and the examiner is seated behind the subject. The subject is instructed to slowly bend forward until the spinal deformity is most prominent, with the apex of the hump aligned with the examiner's line of sight. A scoliometer (Orthopedic Systems INC, Union City, California, USA) is placed on the spinous process at the apex of the curve, and the ATR angle is recorded.
                                                                                                                                                                                                                                                 |
| 
The changes in pelvic tilt angle during the gait cycle between baseline and the 6-month follow-up.
 | 
Pelvic coronal plane asymmetry negatively impacts the gait of patients with AIS. The pelvic tilt angle during the gait cycle is measured using the MOVIT Gait System (Sensor Medica s.r.l., [name]). Changes in this angle from baseline to the 6-month follow-up are utilized to assess improvements in pelvic tilt. Four representative time points within the gait cycle are selected for analysis, corresponding to the minimum and maximum values during the stance phase, and the minimum and maximum values during the swing phase. The validity and reliability of the MOVIT Gait System have been established.
 |
| 
Engagement
                                                                                         | 
The assessment of engagement will be conducted through the following metrics: (i) adherence to home-based exercise performance, including the frequency of over-corrective exercises per week, the duration of over-corrective exercises per week, and the number of individuals in both groups who consistently practice self-correction exercises daily; (ii) dropout rates. Data for the DCG will be automatically collected by the HIRS system, while CIG data will be manually recorded by individuals or their patients.
                                                                                                                                                                 |

---

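### The Cobb response categories for secondary outcome (4) leave reductions above 5° up to and including 6° in no band and count zero change as mild improvement

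*Protocol*

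**What the plan says.** Protocol section 3.2 lists, as secondary outcome (4), the patients with progression and with improvement of the major curve. The table under section 3.3 (Study secondary outcomes) sets the bands:

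- Mild and substantial improvement: "a reduction in the primary curve Cobb angle of 0° to 5° as 'mild improvement,' a reduction of more than 6° as 'substantial improvement".
- Progression, with no lower limit on its size: "an increase in the primary curve Cobb angle as 'progression".

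The same table compares patients "in the DCG and CIG groups in terms of progression, 'mild improvement,' and 'substantial improvement". It names no fourth category.

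Three other statements bear on the point. Section 3.3 says of the two readers' values: "The final Cobb angle will be the average of the two measurements". Section 4.3 says that the proportion of patients who "exhibited disease progression or improvement in Cobb angle between the two groups was compared using the Chi-square test", and it puts the minimal clinically important difference for Cobb improvement at 3.50°. Section 4.4 assumes an SD of 6° for the improvement in each group.

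**The concern.** A set of response categories should give every patient exactly one label. This set does not, and two of its boundaries are badly placed.

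- The upper edge of mild improvement (5°) and the lower edge of substantial improvement (above 6°) do not meet. The patients between them have responded well by the protocol's own standard of 3.50°. They either fall out of the three-way table or have to be placed by a rule that the protocol does not state.
- Zero lies inside the mild band, so a curve that has not moved is reported as improved.
- Progression starts at any increase. A very small recorded increase and a large one get the same label, and no stable category separates them from improvement.

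At stake is how one secondary outcome reads: the counts per category, and any between-group comparison built on all three.

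**Working it through.** **Step 1: do the bands cover every value?** Write X for the reduction in degrees, negative for an increase.

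| Value of X | Label in the protocol |
|---|---|
| X < 0 | progression |
| X = 0 | mild improvement |
| 0 < X ≤ 5 | mild improvement |
| 5 < X ≤ 6 | none |
| X > 6 | substantial improvement |

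Whole-degree readings do not close the gap, because 6 is not more than 6. Averaging two readers makes a value such as 5.5° possible even if each reads whole degrees. Section 4.3 also plans multiple imputation, and imputed changes need not be whole degrees.

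**Step 2: how many patients fall in the gap?** The protocol gives no figure to reproduce, so this is a projection.

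- SD of the reduction: 6° (section 4.4).
- Mean reduction m: not given per group. Assumed to be 0°, 2° or 4°.
- Shape: assumed normal.
- Patients: 128 enrolled or 102 evaluable (section 4.4).

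Formula: P(5 < X ≤ 6) = Φ((6 − m)/6) − Φ((5 − m)/6).

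| m | Calculation | Share | Of 128 | Of 102 |
|---|---|---|---|---|
| 0° | 0.8413 − 0.7977 | 4.4% | 5.6 | 4.5 |
| 2° | 0.7475 − 0.6915 | 5.6% | 7.2 | 5.7 |
| 4° | 0.6306 − 0.5662 | 6.4% | 8.2 | 6.6 |

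The recording scale matters little. On a half-degree grid (5.5° and 6.0° unclassified) the shares are 4.2%, 5.5% and 6.4%. On whole degrees (6° alone) they are 4.0%, 5.3% and 6.3%. Over a wider range of means, −2° to 8°, the continuous-scale share runs from 3.0% to 6.6%.

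**Step 3: is the loss uneven between groups?** Take means of 0° and 4°, which differ by the 4° assumed in section 4.4, with 64 patients per group. The expected losses are 0.0437 × 64 = 2.8 and 0.0644 × 64 = 4.1, a difference of 1.3 patients.

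**Step 4: how many have exactly zero change?** This depends on the recording scale, which the protocol does not state. For m from 0° to 4°, the share recorded as exactly 0° is 2.7% to 3.3% on a half-degree grid and 5.3% to 6.6% on whole degrees.

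**Step 5: the progression boundary.** If the true change is zero and the error is symmetric and continuous, half of such curves are recorded as increases whatever the error SD. That follows from placing the cut at zero. The protocol states neither the measurement error nor how many curves are truly unchanged, so the number of patients affected cannot be derived.

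**The case against.** The strongest reply is that little depends on this. It is the last-listed secondary outcome. The primary outcome is the mean change in Cobb angle, compared by t-test, and neither that test nor the sample size uses the bands. This stands, and it limits the weight of the point.

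Second, a reader might infer that the chi-square test itself loses patients. The documents do not settle that. Section 4.3 and the list in section 3.2 speak of progression and improvement as a pair. On a two-way split, a reduction of 5.5° or 6° is plainly improvement and nobody is lost. The gap is certain only for the three-way comparison in the outcome table. Pooling would still leave zero change counted as improvement.

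Third, above 6° may be loose wording for 6° or more. With whole-degree values that would close the gap. With half-degree values 5.5° would still be unclassified: Φ((5.75 − m)/6) − Φ((5.25 − m)/6) is 2.2% at m = 0° and 3.2% at m = 4°. The text as written supports neither repair.

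Fourth, section 4.3 reports that another trial counted absence of progression as treatment success, so grouping no change with the favourable results has some basis. That supports the grouping, but it does not justify calling an unchanged curve improved.

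Finally, the chi-square test ignores the order of the categories. This costs some power but is not an error, and the point does not rest on it.

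**Conclusion.** The point holds as a defect in a stated definition. The bands are not exhaustive, and they label no change as improvement. Nothing elsewhere in the protocol repairs this.

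About 4% to 6% of patients would be unclassified in the three-category comparison, that is about 5 to 8 of 128 enrolled or 4 to 7 of 102 evaluable. This rests on the protocol's SD of 6°, an assumed mean reduction of 0° to 4°, and a normal distribution. The imbalance between groups is likely to be small, on the order of one patient.

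A reader might go further and infer that the progression and improvement proportions cannot be interpreted because reading error swamps them. The documents do not support that. They give no measurement error, the even split in step 5 applies only to curves with no true change, the same cut applies to both groups, and two readings are averaged. What can be said is that a zero threshold lets reading error decide the label of an unchanged curve, to an extent that cannot be derived here.

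**What to change.** Before data lock, amend the outcome table so that the bands are contiguous and exhaustive:

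- Substantial improvement: a reduction of more than 5°.
- Mild improvement: a reduction above 0° and up to and including 5°.
- No change: exactly 0°, as a separate category.
- Progression: an increase. If the sponsor wants a minimum increase, it should justify the value against measurement error and extend the no-change category to meet it, so that no new gap opens.

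In section 4.3, state whether the chi-square test uses the full set of categories or a two-way split, and if two-way, on which side no change falls.

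One partial repair should be avoided: taking 0° out of mild improvement without adding a no-change category would only move the gap from 6° to 0°.

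The cost is a change of wording, with no new data and no effect on the sample size or the primary analysis. The unclassified share becomes 0%. The downside is that slightly fewer patients are called improved, namely those with exactly zero change.
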